### Statistical analysis

The variables that reflect walking capacity, community participation and quality of life will be analysed by pairwise comparisons between the three groups using the Students' t-test, or Wilcoxon's rank-sum test if it is clearly not normally distributed.

The other health variables: number of falls, number of readmissions to hospital, comorbidities, and number of visits to the doctors will be expressed as a proportion of events per person and analysed by pairwise comparisons between the three groups using the Chi square test.

To ascertain the threshold of post-intervention walking speed that results in the maintenance of 80% of predicted 6-min distance at 12 months, receiver operating characteristic (ROC) curves will be constructed. Youden's Index will be used to determine the cut-off point for walking speed at the end of the programs that gives the best combination of specificity and sensitivity.

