### Randomisation

Randomisation will be computer-generated, independent and concealed. Participants will be recruited in cohorts of 15. Each cohort will be ranked in descending order according to comfortable walking speed over 10 m and then organized into matched triplets. The participants in each triplet will then be assigned to Group A or B or C by random allocation generated by computer in order to provide secure randomisation, concealed from the recruiter. In this way, participants will be stratified according to initial level of walking disability since this has been found to affect outcome [18].

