### Measurement

Since the main aim the study is to improve community ambulation, the primary outcome will be walking capacity measured as the distance covered during the 6-minunte walk test at 12 months. Given the hypothesis that improving walking capacity will directly lead to improvements in health and community participation, the secondary outcomes measures will include measures of health and community participation as well as a measure of walking quality.

Therefore, the outcome measures will be:

• Walking

Walking capacity will be assessed using the 6-minute Walk Test (distance covered in 6 min). Walking quality will be assessed using the 10-metre Walk Test (speed, stride length, cadence).

• Health

Health will be assessed by recording number of falls, number of readmissions to hospital, number of comorbidities, number of visits to the doctor, and quality of life (Euroqol EQ-5D score).

• Community participation

Community participation will be assessed using a self-efficacy questionnaire about walking ability, based on the Falls Efficacy Scale [19] and the Adelaide Activities Profile [20].

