### Sample size

210 participants will be recruited. The sample size has been calculated to reliably detect a treatment effect size of a 50 m difference in walking capacity with 80% power at a two-tailed significance level of 0.05 on any pairwise comparison. This effect size has been derived from the walking capacity of a population of community-dwelling stroke patients who took part in the previous treadmill walking program [17]. On entry to this randomised controlled trial, the distance walked in 6 minutes was 280 (SD, 100) m using the same measurement procedure to the present proposal. The smallest number of participants to detect a 50 m difference between two groups estimated from independent samples is 63 participants per group, i.e., 189 participants in total. On the assumption that about 10% of the participants may drop out during the course of the study, we have set a target of 210 participants in total.

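### Arms are randomised within speed-matched triplets but compared with an unpaired t-test, so the primary test is conservative and gives up power it could keep

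*Protocol article*

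**What the plan says.** - **Protocol article, Randomisation.** On intake, the section states: "Participants will be recruited in cohorts of 15". It describes the matching as follows: "Each cohort will be ranked in descending order according to comfortable walking speed over 10 m and then organized into matched triplets". Allocation is made inside these sets: "The participants in each triplet will then be assigned to Group A or B or C by random allocation generated by computer". The reason given is that "participants will be stratified according to initial level of walking disability since this has been found to affect outcome".
- **Protocol article, Measurement.** "the primary outcome will be walking capacity measured as the distance covered during the 6-minunte walk test at 12 months".
- **Protocol article, Statistical analysis.** For the outcomes on walking, participation and quality of life, the text says that they "will be analysed by pairwise comparisons between the three groups using the Students' t-test". The fallback is worded "or Wilcoxon's rank-sum test if it is clearly not normally distributed". The section gives these comparisons no term for triplet, cohort, baseline speed or baseline distance.
- **Protocol article, Sample size.** The smallest number needed for a 50 m difference, "estimated from independent samples is 63 participants per group", is raised to 210 in total for 10% dropout.

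The Statistical analysis section does not say whether the t-test is paired. The unpaired reading follows from the fallback, since the rank-sum test compares independent groups, and from the independent-samples basis of the sample size.

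**The concern.** Matching on a factor that predicts outcome makes the arm means positively correlated: a triplet of fast walkers raises all three arms together, and a slow triplet lowers all three. The true variance of a difference between two arms is then smaller than the unpaired formula gives. By the article's own account the matching factor is prognostic, so this correlation is expected to be present.

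The trial accepts the logistics of recruiting in cohorts of 15 to balance walking speed, then names a test whose standard error ignores that balance. P-values come out too large. The risk is a false finding of no difference, above all for 4 months against 2 months of training, where both arms are active and the difference may well be under 50 m.

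**Working it through.** **Inputs from the documents.** SD 100 m, difference 50 m, two-sided 0.05, 80% power, 10% dropout, 210 participants (Sample size). Cohorts of 15, which gives 14 cohorts, 5 triplets per cohort and 70 triplets in all (Randomisation).

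**Assumed input.** The correlation r between baseline speed and 12-month 6-minute distance is not given. The range 0.5 to 0.8 is shown.

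**1. The plan's own figure.** n per group = 2 × [(1.96 + 0.8416) × 100 / 50]² = 62.8, so 63. Then 3 × 63 = 189, and 189 / 0.9 = 210. The stated sample size reproduces.

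**2. Standard error used by the unpaired test.** With 63 completers per arm, SE = 100 × √(2/63) = 17.8 m. The critical t on 124 df is 1.979, so a difference must exceed 1.979 × 17.82 = 35.3 m to be significant.

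**3. True standard error under the triplet scheme.** Let ρ be the within-triplet correlation of the outcome. Simulating the ranking of cohorts of 15 gives ρ of about 0.22, 0.43 and 0.56 for r = 0.5, 0.7 and 0.8. With all triplets intact, the variance of the difference is 2 × SD² × (1 − ρ)/n. If 10% drop out at random, about 70 × 0.9 × 0.9 = 56.7 triplets still contribute to both arms. The factor becomes 1 − ρ × 56.7/63 = 1 − 0.9ρ.

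- r = 0.5: 17.82 × √(1 − 0.9 × 0.22) = 16.0 m
- r = 0.7: 17.82 × √(1 − 0.9 × 0.43) = 14.0 m
- r = 0.8: 17.82 × √(1 − 0.9 × 0.56) = 12.5 m

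**4. Actual error rate.** This is 2 × Φ(−35.27 / true SE). Simulation of the full scheme (70 triplets, 10% random dropout, SD 100) was run separately.

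| r | Formula | Simulation |
|---|---|---|
| 0.5 | 2.7% | 2.8–3.1% |
| 0.7 | 1.1% | 1.3% |
| 0.8 | 0.5% | 0.5–0.6% |

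At r = 0 the simulated rate is about 5%, as it should be. A model with baseline speed as covariate held about 5% throughout. So did a within-triplet test when no one dropped out.

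**5. Power.** For the unpaired test, power for a difference d is Φ((d − 35.27) / true SE). For the model with speed, SE = 17.82 × √(1 − r²), which is 15.4 m at r = 0.5 and 12.7 m at r = 0.7, and power is Φ(d/SE − 1.979). Simulation results are in brackets.

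| Difference | r | Unpaired t-test | Model with speed |
|---|---|---|---|
| 50 m | 0.5 | 82% (81–82%) | 90% (89%) |
| 50 m | 0.7 | 85% (84–85%) | 97% (97–98%) |
| 25 m | 0.5 | 26% (27%) | 36% (38%) |
| 25 m | 0.7 | 23% (23–24%) | 49% (49–50%) |

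The 25 m rows are illustrative; the protocol names no such target. For 50 m, stronger matching raises the power of the unpaired test. For 25 m, which is below the 35.3 m threshold, stronger matching lowers it.

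**6. Interval width.** A 95% interval from the unpaired test has half-width 35.3 m. The model with speed gives about 1.979 × 15.43 = 30.5 m at r = 0.5 and 1.979 × 12.72 = 25.2 m at r = 0.7.

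**The case against.** The strongest reply is that the error is only conservative. The 5% level holds as an upper bound, so this mechanism cannot create a false claim of benefit. With 1:1:1 allocation inside triplets, the difference in arm means stays unbiased. The power promised for 50 m is met, and 210 participants remain enough. All of this stands, and it limits how serious the point is.

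A reader might infer more in four ways, and the documents do not support any of them:

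- **That the matching is wasted.** It is not. The true variance still falls and the arms stay balanced on speed, which is why the unpaired test has more than 80% power for 50 m. Only the part that a correct standard error would recover is lost.
- **That the trial's stated confidence intervals are wrong.** The article states none for this trial. The remark on width applies to any interval later derived from the same t-test.
- **That the trial is underpowered for its target.** The figures above show otherwise.
- **That the loss is known to be large.** It depends on r, which the documents do not give. Restricting entry to speeds below 1 m/s narrows the speed range and could lower r.

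It can also be said that covariates are commonly left to an analysis plan that is not shown. That answers a silent protocol. This one names the test, and the test does not match the design it describes.

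**Conclusion.** The named analysis does not respect the named randomisation, and this should be fixed. The unpaired standard error is about 12% too large at r = 0.5 (17.8/16.0) and 28% too large at r = 0.7 (17.82/13.95). The nominal 5% test then runs at about 3% and 1.3%, and at 0.5% if r = 0.8. The cost for 50 m is about 8 percentage points of power at r = 0.5 (81% against 89%) and 12 at r = 0.7 (85% against 97%). At 25 m with r = 0.7, about half the power is lost.

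This rests on three assumptions: the t-test is unpaired, dropout is random at 10%, and r lies in the range shown. The effect vanishes only if baseline speed does not predict 12-month distance, which is contrary to the article's own reason for matching. The point is about precision and calibration; it does not cast doubt on a positive result.

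**What to change.** In the Statistical analysis section:

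1. Replace the t-test for the primary outcome by a linear model of 12-month 6-minute distance on group, with baseline 10-m speed as covariate and either cohort as a further covariate or triplet as a random effect. Report the three pairwise group differences from this model. Unlike a strictly paired test, it keeps participants whose triplet is broken by dropout.
2. Use the same model for the other continuous outcomes.
3. Replace the rank-sum fallback by a permutation test within triplets.
4. Fix the choice before unblinding, so that adjustment cannot look data-driven.

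Only the version with baseline speed alone was checked for power; the cohort and random-triplet forms follow from the same reasoning. Speed, cohort and triplet are already produced by the randomisation, so the change needs no extra participants, visits or data. The sample size can stay at 210.

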## Methods/Design

A prospective, randomised controlled trial will be carried out (Figure 2). It will include concealed randomisation, blinded assessment and intention-to-treat analysis. 210 participants will be recruited and randomly allocated into either Group A (walking training 3 times per week for 4 months), Group B (walking training 3 times per week for 2 months) or Group C (no active intervention). Outcome measures will be collected at baseline, 2 months, 4 months, 6 months and 12 months. Both data collection and data analysis will be completed by a researcher who is blinded to group allocation. The study has obtained ethical approval from the appropriate Human Research Ethics Committees.

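### The named primary test uses neither the baseline 6-minute distance nor the speed-matched triplets, so it is valid but less precise than the collected data allow

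*Protocol article*

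**What the plan says.** The Measurement section states that "the primary outcome will be walking capacity measured as the distance covered during the 6-minunte walk test at 12 months". This is the distance itself; no change from baseline is mentioned. The Statistical analysis section compares walking capacity between each pair of groups "using the Students' t-test, or Wilcoxon's rank-sum test if it is clearly not normally distributed", with no covariate and no stratification factor.

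The same measure exists before treatment. Under Methods/Design, "Outcome measures will be collected at baseline, 2 months, 4 months, 6 months and 12 months".

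Under Randomisation, cohorts of 15 are ranked on comfortable walking speed, formed into matched triplets and randomised within triplet. The reason given is that initial walking disability has been found to affect outcome.

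The Sample size section targets "a 50 m difference in walking capacity with 80% power at a two-tailed significance level of 0.05 on any pairwise comparison". It takes its SD from an earlier trial, in which at entry "the distance walked in 6 minutes was 280 (SD, 100) m". The requirement "estimated from independent samples is 63 participants per group, i.e., 189 participants in total" is then raised to 210 for 10% dropout.

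**The concern.** The between-person SD of 100 m is twice the 50 m target. Much of that spread is probably already visible at baseline, because people who walk far at entry tend to walk far a year later. A two-sample test on the 12-month value leaves all of it in the error term.

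The plan also treats initial walking ability inconsistently. It is prognostic enough to determine how participants are randomised, yet it does not enter the analysis. Matching makes the groups more alike than chance would, but the two-sample standard error does not reflect this and comes out too large.

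Finally, no criterion is given for when the distribution is far enough from normal to change the test. The primary method therefore depends on the outcome data.

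At stake is the precision of all three pairwise comparisons. The 4- versus 2-month comparison in objective (i) may matter most, because a difference between two active arms could be smaller than 50 m. The article does not say that it is.

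**Working it through.** **Inputs from the article.** Difference 50 m, SD 100 m, two-sided 0.05, power 80%, 63 per group, dropout 10% (Sample size); matched triplets in cohorts of 15 (Randomisation).

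**Assumptions not in the article.** The baseline-to-12-month correlation r is shown for 0.5 to 0.8. A smaller true difference of 25 m is used for illustration. The entry SD of 100 m is taken to hold at 12 months, as the article's own calculation does.

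**Step 1: reproduce the plan.** n per group = 2 × (1.960 + 0.842)² × 100² / 50² = 62.8, so 63. Then 3 × 63 = 189, and 189 / 0.90 = 210. The stated figures reproduce. Power with 63 per group is 80.1% by the normal approximation and 79.5% by the exact t calculation.

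**Step 2: add baseline adjustment, simple randomisation.** Residual SD = 100 × √(1 − r²). Standard error = residual SD × √(2/63), where √(2/63) = 0.178. Power ≈ Φ(difference / SE − 1.960). Half-width ≈ 1.98 × SE.

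| r | Residual SD (m) | Power, 50 m | Power, 25 m | 95% CI half-width (m) | Detectable at 80% power (m) |
|---|---|---|---|---|---|
| unadjusted | 100 | 80.1% | 28.9% | 35 | 49.9 |
| 0.5 | 86.6 | 90.0% | 36.7% | 31 | 43.2 |
| 0.6 | 80.0 | 93.9% | 41.8% | 28 | 39.9 |
| 0.7 | 71.4 | 97.6% | 50.2% | 25 | 35.6 |
| 0.8 | 60.0 | 99.7% | 64.7% | 21 | 30.0 |

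Power forgone at 50 m is 90.0 − 80.1 = 9.9 to 99.7 − 80.1 = 19.6 points. At 25 m it is 36.7 − 28.9 = 7.8 to 64.7 − 28.9 = 35.8 points.

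**Step 3: share of attainable power kept.** At 50 m, 80.1 / 90.0 = 89% (r = 0.5) and 80.1 / 99.7 = 80% (r = 0.8). At 25 m, 28.9 / 36.7 = 79%, 28.9 / 41.8 = 69%, 28.9 / 50.2 = 58% and 28.9 / 64.7 = 45% for r = 0.5, 0.6, 0.7 and 0.8.

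**Step 4: matched triplets.** Simulation of 13 cohorts of 15 (65 per group), randomised within speed-ranked triplets, with an assumed correlation of 0.8 between baseline speed and baseline distance and 3,000 trials per setting. The ANCOVA adjusts for baseline distance only.

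| True difference | r | t-test rejects | ANCOVA rejects |
|---|---|---|---|
| 0 m | 0.7 | 2.2% | 5.8% |
| 0 m | 0.8 | 1.7% | 5.3% |
| 25 m | 0.7 | 27.6% | 51.5% |
| 25 m | 0.8 | 24.9% | 65.8% |
| 50 m | 0.7 | 85.5% | 98.1% |
| 50 m | 0.8 | 85.6% | 99.8% |

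The Monte Carlo standard error near 2% is √(0.022 × 0.978 / 3000) = 0.3 points, so the t-test's type I error lies at about 1 to 3%. Near 5% the standard error is 0.4 points, so the ANCOVA figures are within about two standard errors of nominal. With a smaller r or a weaker speed-distance correlation, the t-test would be less conservative.

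**The case against.** The strongest reply is that nothing here is wrong. An unadjusted two-sample t-test is a valid analysis of a randomised trial, it matches the independent-samples basis of the sample size, and the stated numbers reproduce. The article is also condensed, and an analysis plan that is not shown might add covariates. The first part stands: this is a gain in efficiency and not a flaw in validity. The second carries less weight, because the article names the test and so makes a choice.

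Four stronger readings are tempting, and the documents do not support them.

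- *The plan gives away most of the attainable power for 4 versus 2 months.* The article applies 50 m to any pairwise comparison, and there the t-test keeps 80 to 89% of the attainable power. Losing more than half needs r of about 0.8 or more and a true difference well below 50 m (about 12 to 31 m at r = 0.8). The article gives neither.
- *Chance imbalance in baseline distance is left uncontrolled.* Matching on speed limits it to the extent that speed tracks distance. For the same reason, the gain at 50 m is smaller in the simulation (98.1 − 85.5 = 12.6 points at r = 0.7) than under simple randomisation (97.6 − 80.1 = 17.5).
- *A rank test gives nothing in metres and cannot use a covariate.* A Hodges-Lehmann shift is in metres, and rank ANCOVA and the van Elteren test accommodate covariates or strata. The fair complaint is that the test as named uses neither.
- *The analyst could choose the favourable test.* Methods/Design has the analysis done by someone blinded to allocation. The switching rule remains loose, but it is not an unblinded choice.

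**Conclusion.** The point holds as a loss of efficiency in a stated method. The named test ignores both the baseline 6-minute distance and the matched triplets, although the trial collects the first and randomises by the second. For r between 0.5 and 0.8 and simple randomisation, adjustment would cut the error variance by r², that is by 25 to 64%. The cost is about 10 to 20 points of power at 50 m and about 8 to 36 points at an assumed 25 m. Under the matched design the t-test is conservative rather than anti-conservative, so a positive result would not be in doubt; a real but smaller difference is what could be missed.

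The direction is secure. The size rests on r, the 25 m scenario, the SD carrying over to 12 months and, for the type I error, the speed-distance correlation of 0.8. All but the entry SD itself come from outside the article. The planned 80% power at 50 m is not in question.

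**What to change.** Before unblinding, name one primary analysis: ANCOVA of 12-month 6-minute distance on group, with baseline 6-minute distance and the matching factor as covariates. Report the adjusted mean differences in metres with 95% confidence intervals for the three pairwise comparisons. The matching factor can be baseline walking speed or triplet; continuous speed is simpler and copes more easily with triplets broken by dropout.

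Replace the conditional switch of the primary test with a rank-based or permutation analysis specified in advance as a sensitivity analysis.

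Apply the same baseline adjustment to the other continuous outcomes measured at baseline. Where scores may be bounded or skewed, such as EQ-5D and the questionnaires, add a robust or bootstrap check.

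The cost is a change of wording and modest extra modelling. It needs no extra recruitment, visits or measurements, and the sample size can stay at 210.

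### Falls, readmissions, comorbidities and doctor visits are to be expressed as a proportion that is really a rate and compared by chi-square, which is invalid if events are the unit counted

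*Protocol article*

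**What the plan says.** In the Measurement section of the protocol article, health is assessed by "recording number of falls, number of readmissions to hospital, number of comorbidities, number of visits to the doctor", together with a quality-of-life score. The first four are counts for each participant. They are secondary: "the secondary outcomes measures will include measures of health and community participation as well as a measure of walking quality".

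The Statistical analysis section then fixes both the summary and the test for these four variables: they "will be expressed as a proportion of events per person and analysed by pairwise comparisons between the three groups using the Chi square test". The same section allows a rank-sum test when data are clearly not normal, but only for walking capacity, community participation and quality of life. No fallback covers the four counts, and no method for repeated events within a person is named.

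**The concern.** A proportion needs a numerator that is a subset of its denominator. Events are not a subset of persons: one person can fall three times, so events divided by persons can exceed 1. The stated summary is therefore a rate under the name of a proportion.

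A chi-square test needs independent units, each counted once. If the units are events, a person who falls often contributes several that are not independent. Whenever people differ in their underlying rate, the arm totals vary more than the test assumes and the p-values come out too small.

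Four health outcomes in three pairwise comparisons make 12 tests under this rule. Health is named in the trial's first objective, and falls and readmissions also bear on safety. A chance difference between training and control could be reported as benefit or harm.

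This is a stated rule that does not work as worded, not a detail left to a fuller document.

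**Working it through.** **Inputs from the document.** The Sample size section states "a treatment effect size of a 50 m difference in walking capacity", "the distance walked in 6 minutes was 280 (SD, 100) m", "with 80% power at a two-tailed significance level of 0.05 on any pairwise comparison" and "63 participants per group, i.e., 189 participants in total".

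**Reproducing the plan's own figure.** n per group = 2 × (1.960 + 0.842)² × (100/50)² = 2 × 7.85 × 4 = 62.8, so 63. Then 3 × 63 = 189, and 189/0.90 = 210. The sample size reproduces. It concerns walking distance only; no rate, dispersion or power is given for the counts.

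**Assumptions.** 63 analysed per arm and no true difference. Counts have mean μ per person and variance μ + kμ², where k = 0 is Poisson and k > 0 is negative binomial. All persons are observed equally long. Both μ and k are assumed and are varied over a range.

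**Construction A: chi-square on event totals.** With totals a and b in equal arms, the statistic is (a − b)²/(a + b). It takes the variance of a − b to be 2nμ, whereas the true variance is 2nμ(1 + kμ). The ratio is φ = 1 + kμ, so type I error = 2[1 − Φ(1.96/√φ)], whatever n is. Simulation used 20,000 replicates, with a Monte Carlo standard error near 5% of √(0.05 × 0.95/20,000) = 0.15 percentage points.

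| μ | k | φ | 1.96/√φ | Formula | Simulated |
|---|---|---|---|---|---|
| 0.3 | 0 | 1.0 | 1.960 | 5.0% | 5.0% |
| 0.3 | 1 | 1.3 | 1.719 | 8.6% | 8.6% |
| 1 | 0.5 | 1.5 | 1.600 | 11.0% | 10.9% |
| 1 | 1 | 2.0 | 1.386 | 16.6% | 16.7% |
| 2 | 1 | 3.0 | 1.132 | 25.8% | 25.3% |
| 5 | 1 | 6.0 | 0.800 | 42.4% | 42.2% |

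**Construction B: events over persons forced into a 2×2 table.** The test takes the variance per person to be μ(1 − μ). Even for Poisson counts the true variance is μ, so the ratio is 1/(1 − μ) and type I error is about 2[1 − Φ(1.96√(1 − μ))].

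- μ = 0.3: 1.96 × √0.7 = 1.640, giving 10.1% (simulated 10.1%).
- μ = 0.5: 1.96 × √0.5 = 1.386, giving 16.6% (simulated 18.3%; the approximation ignores variation in the pooled proportion).
- μ = 1: at least one arm has more events than persons in about 71% of simulated trials, so the table cannot be formed.
- μ = 2: this happens in essentially every trial.

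**Construction C: persons with at least one event.** Each person counts once. Simulated type I error lies between 0.1% and 6.1% over all scenarios (μ from 0.3 to 5, k from 0 to 3). The 0.1% arises at μ = 5 with k = 0, where almost everyone has an event and the test says next to nothing.

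**Other analyses with the person as unit.** A t-test on per-person counts gives 4.4% to 5.2% in all scenarios. Negative binomial regression gives 5.5% to 5.9% in the three scenarios fitted (1,000 replicates each, Monte Carlo standard error √(0.05 × 0.95/1,000) = 0.7 percentage points).

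**The case against.** The strongest reply is that the phrase does not determine the test. A proportion compared by chi-square also fits a table of persons, with and without an event, and on that reading the test is sound (at most 6.1%). This stands as a possible meaning. It does not rescue the sentence, because the text speaks of events for variables recorded as numbers and never says that they are reduced to persons with any event. An analyst following the words could build construction A or B.

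The second reply is that the inflation on event totals is assumed, not shown. That also stands in part. With exactly Poisson counts the error is about 5%, and for rare events such as readmissions might be it may be modest. Heterogeneity between persons is plausible for falls and visits, but the article gives no figures.

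Several stronger inferences are tempting and are not supported:

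- **All four outcomes will have p-values that are too small.** This is not shown for comorbidities, which are a per-person tally rather than recurrent events and could be under-dispersed. Nor does it hold where the literal table cannot be formed, since there is then no p-value.
- **Early leavers get the same denominator as completers.** The article does not say how time observed enters the denominator, and a condensed article may leave that to a fuller document.
- **Ignoring comorbidities at entry invalidates the comparison.** Under randomisation this costs precision, not validity.

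**Conclusion.** The point holds in conditional form. The stated summary is not a proportion, and chi-square is invalid if events are the unit counted. On event totals, type I error at a nominal 5% runs from about 5% (Poisson) to 42% (mean 5, dispersion 1), with 16.6% at mean 1 and dispersion 1. The literal table of events over persons gives 10% at mean 0.3 and 18% at mean 0.5 even for Poisson counts, and often fails altogether from mean 1 upwards. These figures depend on assumed means and dispersions with 63 per arm and equal observation time; none comes from the document.

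A reader might infer that the trial's main conclusion is at risk. It is not: the primary outcome is the 6-minute walk distance at 12 months, and its analysis, the sample size and the walking-speed threshold analysis are untouched. This is a should-fix on secondary outcomes.

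**What to change.** Replace the sentence on the four health counts with wording that makes the person the unit:

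- **Falls, readmissions and doctor visits:** negative binomial regression, or Poisson regression with robust variance, with the log of time observed as offset. Report rate ratios with 95% confidence intervals for each pairwise comparison.
- **Chi-square:** keep it only for the proportion of persons with at least one event, and say so explicitly.
- **Comorbidities:** compare as a per-person count, for example by rank-sum test. Adjustment for the baseline count is optional and would be made for precision.

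If persons with at least one event was the intended measure all along, one sentence saying so makes the planned test acceptable. It would discard the repeat events and would tell little about doctor visits if nearly everyone has one.

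The cost is a change of analysis wording and slightly more analysis work. No further participants or outcome measures are needed. The offset does require each person's time under observation; the article does not say that individual dates are recorded, so this should be confirmed. For over-dispersed counts, p-values will usually be less extreme than from chi-square on event totals.
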